## Abstract

**Background:**

Stroke is ischemia and neurological dysfunction caused by acute brain circulation loss. It causes acute localized neurological abnormalities such as weakness, sensory deficit, or language issues that require long-term treatment. These deficiencies harm the patient and their family psychologically, socially, and economically. Thus, combination treatment can rapidly rehabilitate such patients. Detoxification methods like Ayurvedic medicated enema help stroke pathophysiology. Physical modalities in physiotherapy have been shown to facilitate normal movement and function on the stroke patient’s affected side, increasing independence with everyday duties. A stroke patient may benefit from
*Dashmoola Niruha Basti*, Function Electrical Stimulation (FES), and Motor Relearning Programme (MRP).

**Aim & Objectives:**

This study compares the adjuvant role of
*Dashmoola Basti* with MRP and FES in stroke recovery. The main goals of this study are to assess and compare the adjuvant role of
*Dashmoola Basti* with standard control over sensorimotor function of lower extremities, static and dynamic balance in stroke patients; gait parameters; resistance experienced during passive range of motion; quality of life of patients; Barthel Index; Modified Ashworth Scale; and Fuglmeyer assessment, Single Limb Stance Test, Functional Reach Test.

**Methods:**

A total of 40 patients will be enrolled and divided randomly into two equal groups. In Group A (control), standard treatment (modern + physiotherapy) will be prescribed for one month. In Group B (interventional group),
*Dashmoola Basti* will be added to the aforementioned standard treatment for one month.

**Expected results:**

Improvement in Fuglmeyer assessment, Single Limb Stance Test, Functional Reach Test, quality of Life of Patients, Barthel Index, Modified Ashworth scale, and National Institute of Health (NIH) stroke-scale-score will be observed and recorded.

**Conclusions:**

Results and conclusions will be derived according to the data collected in case record form and assessment sheets filled at baseline and follow-up visits.

**Trial registration:**

CTRI/2021/10/037445 dated 21.10.2021.

## Introduction

In clinical practice, stroke has been very notorious for impeding the continuity of life and day-to-day activities. It is the most common example of such a crippling disorder. On extensive review of contemporary literature, it is observed that, despite massive worldwide efforts in this science to rectify early results in reducing the risk of death or disability, it is disappointing.
^
1
^ Partial recovery is obtained after a particularly long time. Moreover, it is observed that there are certain limitations, contra-indications, or side effects of currently established treatment modalities for stroke.
^
2
^

Considering the complicated and critical nature of the disease, i.e., stroke, it becomes imperative to search for safe, promising, and effective treatment modalities in alternative sciences for early rehabilitation purposes for stroke. Though most of the studies suggest that the individual use of
*Panchakarma* therapy, external oleation (
*Bahya Snehana*), sudation therapy (
*Swedana*) along with medicated enema (
*Basti*) and conventional physiotherapy, i.e., Motor Relearning Programme (MRP), and the combination of electrical modality with Functional Electrical Stimulation (FES) shows promising results in the rehabilitation of patients with stroke.

However, no study has been carried out to assess their combined effects on the therapeutic outcome of the rehabilitation of such patients. Moreover, the research is also required to determine the MRP and FES combined effect of supporting stroke patients for improving knee extension and gait parameters. Therefore, this study is proposed to generate clinical evidence showing excellent post-stroke recovery within a short time in restoring gross and fine movements to the maximum extent quicker.

The study aims to analyze and compare the adjuvant role of
*Dashmoola Basti* with standard treatment in stroke rehabilitation. In addition, the efficacy of physiotherapy (MRP and FES) in rehabilitating stroke patients will be assessed. The study’s goal is to assess and compare the adjuvant role of
*Dashmoola Basti* with standard control over sensorimotor function of lower extremities in stroke patients using the Fugl-Meyer assessment, as well as to assess and compare the adjuvant role of
*Dashmoola Basti* with standard control over static and dynamic balance in stroke patients using the Single Limb Stance Test and Functional Reach Test, respectively. The secondary goal is to evaluate and compare the adjuvant role of
*Dashmoola Basti* with standard control over gait parameters (distance and time parameters), the Barthel Index, resistance experienced during passive range of motion based on the modified Ashworth scale, and the National Institute of Health (NIH) stroke-scale-score in stroke patients.

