### Study design

It is an interventional study, it is a superiority clinical trial, i.e., randomized reference standard control open-labeled two-arm comparative clinical trial.

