### Interventions

For group A, standard control modern treatment (Anti-thrombotic treatment, e.g. Tab. Ecosprin 75/150 mg OD and Tab. Notropril 800 mg TDS) will be given along with physiotherapy. The physiotherapy sitting for motor relearning program and functional stimulation will be given for 55 mins per sitting, five days weekly for one month.

For group B, standard control modern treatment will be given along with Ayurveda Panchakarma and physiotherapy. In this case, gentle massage with
*Dashmoola Taila* +
*Nadi Sweda* with
*Dashmoola Kwatha* + medicated enema (alternate regime of
*Dashamoola Niruha Basti* with
*Anuvasana Basti* with
*Dashmoola Taila* will be prescribed for the treatment. The alternative regime of medicated enema i.e.,
*Anuvasana Basti* (oil enema) and
*Dashamoola Niruha Basti* (decoction enema) will be given on odd and even days respectively for one month, and physiotherapy for five days weekly for one month.

The study’s methodology is mentioned in
Table 1 and the flowchart of the study design or methodology is given in
Figure 1.

**Table 1. T1:** Methodology of the study.

Group	Sample size	Intervention	Type of Treatment	Duration of treatment	Total duration	Follow-up
**A**	20	Standard Control	Modern + Physiotherapy (MRP+FES)	For Physiotherapy sitting (55 mins/sitting)	Physiotherapy (Five days weekly for one month)	on 60 ^th^ & 90 ^th^ Day
**B**	20	Standard Control + *Panchakarma*	Modern + Physiotherapy (MRP+FES) Gentle massage with *Dashmoola Taila* + *Nadi Sweda* with *Dashmoola Kwatha* + Medicated Enema (Alternate regime of *Dashamoola Niruha Basti* with *Anuvasana Basti* with *Dashmoola Taila*	• Same as group A+ *Dashmoola Basti* Details of *Dashmoola Basti* Are as follows: • Local *Snehana*-10 mins • Local *Swedana*-10 mins or till attainment of *Samyak Swinna Lakshana*, whichever is earlier.	• Panchakarma for complete one month (Day 1 ^st^ – Day 30 ^th^) • Physiotherapy for Five days weekly for one month	on 60 ^th^ & 90 ^th^ Day

* FES – Function Electrical Stimulation, MRP – Motor Relearning Programme.

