*Anuvasana Basti Lakshana*).
^
21
^ Moreover, it also increases the therapeutic outcome of these therapies by improving blood circulation in that local region.

As local massage nourishes the muscular tissue and fomentation with
*Dashmool* decoction, massage instantaneously relieves the extremities’ stiffness, especially muscular tissues. Both these procedures also play an important role in enhancing the speed of rehabilitation of the stroke, resulting in a speedy recovery in cognitive functions hampered in it. According to Ayurveda, vitiation of
*Vata* is the most important factor responsible for inducing impairment of cognitive functions and musculoskeletal movements.
^
22
^ Both procedures used
*Dashmoola* oil and
*Dashmoola* decoction, respectively, to pacify vitiated
*Vata* due to their
*Snigdha* &
*Ushna Guna*. Moreover, both improve the patient’s gait and reduce the dependency of the affected individual on relatives.
^
23
^
^,^
^
24
^ Local massage and fomentation with
*Vata* pacifying medicines improve the patient’s quality of life by building confidence and contributing to inducing expected positive outcomes.
^
25
^

On the other hand, the efficacy of physiotherapy, especially of the “Motor Relearning Program” (MRP) and “Functional Electrical Stimulation” (FES) in the early rehabilitation of the stroke can be justified as follows:

Motor learning theory underpins the Motor Relearning Programme (MRP). Carr and Shepherd claimed that motor control training necessitates anticipatory acts as well as continuing exercise. The motor relearning program is useful for improving a group of post-stroke patients’ balance function and functional performance. It consists of four distinct steps, i.e., to analyze the task and practice the missing component and task with a transference of training. Eight studies suggested that MRP planned for five weeks showed better improvement in functional performance on self-care, instrumental activities of daily living, and integration into the community hospital.
^
26
^

The FES is based on electrical stimulation to the peripheral nerves that innervate the paralyzed muscle to generate action potentials in motor neurons, propagating towards the power and causing its contraction. According to John E.R. 1999
*et al.* and Niu
*et al.*, 2019, it is an excellent recovery tool for motor functions hampered in post-stroke conditions.

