## Conclusion

Shreds of evidence generated from the current study may prove the positive benefits of the use of integrative approach of
*Dashamool Niruha Basti* in
*Panchakarma* added with MRP and FES in physiotherapy, to improve gait and speed of movement, decrease the rate of fall while standing or walking, and improves quality of life of patients having stroke. This treatment protocol may become an effective tool in the rehabilitation of such patients, which may broaden the scope of Ayurveda in neurology.

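### The aim to assess the efficacy of MRP and FES has no comparator, because both arms receive them; the A–B contrast should be named as the effect of the whole Panchakarma package

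*Protocol article*

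**What the plan says.** **The aim.** After stating the main purpose, the adjuvant role of Dashmoola Basti, the Introduction adds: "In addition, the efficacy of physiotherapy (MRP and FES) in rehabilitating stroke patients will be assessed". A little earlier it gives the reason: "Moreover, the research is also required to determine the MRP and FES combined effect of supporting stroke patients".

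**The design.** Study design describes a "randomized reference standard control open-labeled two-arm comparative clinical trial".

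**The arms.** For group A, Interventions says: "The physiotherapy sitting for motor relearning program and functional stimulation will be given for 55 mins per sitting, five days weekly for one month", on top of antithrombotic and other drug treatment. For the other arm: "For group B, standard control modern treatment will be given along with Ayurveda Panchakarma and physiotherapy". Table 1 lists MRP and FES under both groups and describes group B as the group A treatment with more added.

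**What group B adds.** Interventions and Table 1 list massage with Dashmoola oil, sudation with Dashmoola decoction, and oil and decoction enemas on alternate days for one month. The aims and the Abstract call the addition Dashmoola Basti, and the Glossary defines Basti as a medicated enema. The Conclusion narrows it to Dashamool Niruha Basti, one of the two enema types. On massage and fomentation, the Discussion says: "Both these procedures also play an important role in enhancing the speed of rehabilitation of the stroke".

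**The analysis.** Data collection, management, and analysis methods plans paired and unpaired t-tests.

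**The concern.** An efficacy claim needs a group without the treatment, or some other source for what would have happened without it. Here every patient receives MRP and FES, so the between-arm test says nothing about them. The plan does include a paired test, and improvement over 30 days is the only result that could be offered under this aim. Eligibility requires onset less than six months before entry, and all patients take concurrent drugs, so they may improve for reasons unrelated to physiotherapy. A significant before-after change could then be read as physiotherapy efficacy.

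A smaller matter of naming goes with this. The between-arm difference belongs to everything group B adds. If it is reported as the effect of the enema, it credits one component with a result that the protocol's own Discussion says other components help to produce.

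**Working it through.** **1. What each arm's mean change contains.** From Interventions and Table 1, with T = change over time without treatment, D = drugs, P = MRP+FES, M = massage, S = sudation, E = enemas (both types):

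- Arm A: T + D + P
- Arm B: T + D + P + M + S + E

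**2. Between-arm contrast.** B − A = M + S + E. The coefficient of P is 0, so the unpaired test carries no information on physiotherapy. The two rows have rank 2. A quantity is estimable only if adding its row leaves the rank at 2:

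| Quantity | Estimable? |
|---|---|
| P (MRP+FES) | No |
| E (enemas alone) | No |
| M + S + E (whole package) | Yes, equal to B − A |
| T + D + P (change under standard care) | Yes, equal to arm A change |

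None of this depends on the number of patients. Extra therapist contact and open-label expectation travel with M + S + E.

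**3. Size of the extra contact.** Table 1 gives 10 minutes of massage and up to 10 minutes of sudation, with Panchakarma on days 1 to 30. If both are done daily, that is up to 20 × 30 = 600 minutes, or 10 hours, before counting the enemas themselves.

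**4. Within-arm route.** The protocol states no SD, expected change or natural-recovery figure, so there is no plan figure to reproduce. As an illustration, suppose P = 0 and let d be the mean change from T + D divided by the SD of change. For a paired t-test with n = 20 and two-sided 5%, the critical value on 19 degrees of freedom is 2.093 and the noncentrality is d × √20:

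| Assumed d | d × √20 | Probability of significance with P = 0 |
|---|---|---|
| 0.3 | 1.34 | 0.25 |
| 0.5 | 2.24 | 0.56 |
| 0.8 | 3.58 | 0.92 |
| 1.0 | 4.47 | 0.99 |

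All are above 5%, and the value depends heavily on the assumed d. The conclusion in step 2 needs none of these figures.

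**5. The name against the content.** Table 1 places massage and sudation under the details of Dashmoola Basti, and the Discussion calls them mandatory before either enema. The Glossary equates Basti with enema, the Conclusion names only the decoction enema, and the Discussion credits massage and fomentation with benefits of their own for speed of rehabilitation, gait and quality of life. Gait and quality of life are both in the Assessment criteria. The protocol thus uses one term for both the package and a part of it.

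**The case against.** **The physiotherapy aim is peripheral.** It is one added sentence with a rationale before it. The specific goals in the Abstract and Introduction all concern adding Dashmoola Basti, and no outcome, test or decision rule is tied to physiotherapy. The protocol does not say that the A–B comparison would answer it, nor that before-after change will be reported as efficacy. All of this is correct, and it limits the weight of the point. It does not remove it: the sentence states as an aim something the arms cannot deliver, and no analysis plan can supply the missing comparator.

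**A p-value below 5% is not the only criterion.** The analysis section also lists improvements of 20% to 35% on six measures that will count as significant. The table above is therefore not the plan's probability of declaring efficacy. But a percentage improvement within an arm is confounded in the same way.

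**The package is disclosed.** Interventions, Table 1 and the Discussion set out the massage and sudation openly and treat them as preparation for the enema. This stands. A reader might infer that the A–B comparison is itself invalid, or that the trial set out to isolate the enema. The documents support neither: randomisation gives a valid comparison of package plus standard care with standard care alone, and no objective is to separate the enema from its preparation. Only the name is at fault.

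**Falls.** The Conclusion hopes the approach will "decrease the rate of fall while standing or walking", and no listed outcome counts falls. A reader might take this as an objective without an outcome. It is hedged closing prose, so it is only a side remark.

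**Conclusion.** The point holds as a fault in the stated aims. The efficacy of MRP and FES cannot be estimated from this design: no patient goes without them, the effect cancels between arms, and within-arm change cannot be separated from natural recovery and drugs. This follows from the treatment lists and rests on no assumed figure. The illustrative chance of a significant paired test with no physiotherapy effect runs from about 25% to 99% for assumed natural change of 0.3 to 1.0 SD. The documents do not say where in that range the trial would fall.

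The package point is secondary. The A–B contrast is valid for the whole addition, and what needs correcting is its attribution to the enema. The main comparison, sample size, allocation and planned between-arm test are unaffected.

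**What to change.** - Introduction: delete the aim to assess the efficacy of MRP and FES, or restate it as a description of change under standard care, with no efficacy claim and no p-value offered as evidence for physiotherapy. Reword the rationale sentence on their combined effect to match.
- Abstract, aims and Conclusion: state the question as the effect of adding the Panchakarma package (massage, sudation, alternating oil and decoction enemas, and the contact that goes with them) to standard care. If Dashmoola Basti is kept as a short name, define it once as that package and align the Glossary.
- Do not attribute the between-arm difference to the enema, or to the decoction enema, alone.
- Optional: remove the remark on falls from the Conclusion.

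These are wording changes. Treatments, sample size and visits stay as they are. The cost is narrower claims; isolating physiotherapy or the enema would need a different design.

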## Methods

### Ethical considerations

IEC clearance is taken from the Institutional Ethical Committee, Datta Meghe Institute of Higher Education and Research (DMIHER), Wardha. IEC certificate obtained: Ref No. DMIHER (DU)/IEC/2021/279 dated 15.04.2021. The project has been registered with Clinical Trials Registry India (CTRI) (registration number
CTRI/2021/10/037445) dated 21.10.2021).

Written informed consent will be taken from the patient before starting the study. During the study, the confidentiality of each patient will be maintained.

### Study design

It is an interventional study, it is a superiority clinical trial, i.e., randomized reference standard control open-labeled two-arm comparative clinical trial.

### Sample size

Due to practical considerations such as cost, patient inconvenience, judgments not to proceed with an investigation or a lengthy study duration, the number of participants in the study is restricted. So for the phase-I trial, 20 sample size is considered for each group.
^
3
^

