### Variables to be measured

Improvements in the following assessment variables are expected as primary outcomes: Fugl-Meyer assessment for sensory-motor function of lower extremities, one-leg stance test, functional reach test for static and dynamic balance in patients, quality of life scale and Barthel index independent living of patients with Stroke, resistance experienced during passive range of motion based measured on Modified Ashworth scale NIHSS for improvements in clinical features of stroke are expected to be measured.
^
7
^

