### Data collection, management, and analysis methods

For retention of patients, appointment reminders will be scheduled, and question-answering sessions will be planned. The complete follow-up will be mentioned in the patient file, and if patients are required to withdraw or discontinue, the patient file will be closed and maintained for the record purposes.

Observations will be made after the completion of the study, according to the data collected with the help of the following:
I.Case registration form with detailed history and examinationsII.Follow-up assessment proforma

The principal investigator and co-investigator will do data monitoring and coding. Data entry will be done in soft copy and case record form in hard copy. The values will be verified twice before submission in soft copy. Each file of the patient is secured with a specific patient code.

The data obtained will be calculated using the Student’s Paired ‘t’-test and Unpaired ‘t’ test for objective variables with
SPSS statistical software.

*To verify the significance of the results*

Improvements in Fugl-Meyer assessment-35%, one leg stance test-20%, functional reach test-35%, quality of life scale-25%, Barthel index-25% and NIH stroke-scale-score-20% will be considered as significant.

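### Twenty per group is justified only by feasibility under a phase-I label, which does not fit the superiority design and efficacy claim stated elsewhere in the protocol

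*Protocol article*

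**What the plan says.** Study design in the protocol article states that "it is a superiority clinical trial, i.e., randomized reference standard control open-labeled two-arm comparative clinical trial". Sample size, the next section, explains the number by "Due to practical considerations such as cost, patient inconvenience, judgments not to proceed with an investigation or a lengthy study duration" and concludes "So for the phase-I trial, 20 sample size is considered for each group", with one citation. The abstract gives the total: "A total of 40 patients will be enrolled and divided randomly into two equal groups".

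The rest of the article describes an efficacy comparison:

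- The Introduction proposes the study in order to produce evidence of excellent recovery after stroke. It lists comparative efficacy goals on motor function, balance, gait, daily living, spasticity and stroke severity.
- Variables to be measured says "Improvements in the following assessment variables are expected as primary outcomes: Fugl-Meyer assessment for sensory-motor function of lower extremities" and goes on to name seven scales in all.
- The data section plans the "Paired ‘t’-test and Unpaired ‘t’ test for objective variables" and adds "Improvements in Fugl-Meyer assessment-35%, one leg stance test-20%, functional reach test-35%, quality of life scale-25%, Barthel index-25% and NIH stroke-scale-score-20% will be considered as significant".
- The Conclusion says "Shreds of evidence generated from the current study may prove the positive benefits".

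**The concern.** Sample size gives a reason for 20 per group, but it is a feasibility reason under an early-phase label. Nothing else in the article matches that label. No objective concerns safety, tolerability, dose-finding or feasibility, and the study is nowhere called a pilot or exploratory. This is not a complaint that a power calculation was left to another document. The rationale that is stated belongs to a different kind of study from the one described around it.

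What is at stake is the conclusion the trial may draw. If it is read as a superiority trial, a non-significant result may be taken as absence of benefit when power for a moderate benefit was low. A significant result from so small a trial tends to overstate the effect, and the Conclusion is already worded to present it as proof. If it is read as an exploratory trial, the same 40 patients give a useful estimate with a wide interval, and neither misreading need arise.

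**Working it through.** **Can 20 per group be reproduced?** No. The article gives no alpha, sidedness, power, SD or expected between-group difference. The only effect-like figures are the 20% to 35% improvements in the data section. They are not said to be between-group, carry no SD and are not linked to the sample size, so they cannot serve as a target difference.

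**What 20 per group can deliver.**

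From the article: 20 per arm (Sample size), two equal groups (abstract) and an unpaired t-test (data section). Assumed: two-sided alpha of 0.05, normal data and a common SD. Differences (d) are in units of the SD of whatever quantity is tested.

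1. Standard error of the difference: √(2/20) = 0.316 SD.
2. 95% confidence interval half-width: t(0.975; 38) × 0.316 = 2.024 × 0.316 = 0.640 SD. An observed difference must exceed this to reach p < 0.05. If the true effect were 0.5 SD, only estimates above it could be significant.
3. Detectable difference at 80% power, normal approximation: (1.960 + 0.842) × 0.316 = 0.886 SD. With the noncentral t it is 0.909 SD, and 1.052 SD at 90% power. A one-sided 5% test would still need 0.80 SD at 80% power.
4. Power and required size, noncentral t:

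| True difference (SD) | Power with 20 per arm | Needed per arm for 80% | Needed per arm for 90% |
|---|---|---|---|
| 0.3 | 15% | 176 | 235 |
| 0.5 | 34% | 64 | 86 |
| 0.8 | 69% | 26 | 34 |
| 1.0 | 87% | 17 | 23 |

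**Effect of unequal arms.** Assignment of interventions specifies simple randomisation, which does not guarantee 20/20. If it were a fair draw for each of 40 patients, the chance of exactly 20/20 is 12.5%, and the chance of 17/23 or worse is 43%. At 17/23 the half-width is 2.024 × √(1/17 + 1/23) = 2.024 × 0.320 = 0.65 SD, only slightly wider than 0.64.

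**Labels set side by side.** Superiority in Study design, primary efficacy outcomes, a rule for what counts as significant, and language of proof all point to a verdict on efficacy. The phase-I label and the feasibility rationale point to an early-phase estimate. The article does not say which governs the interpretation.

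**The case against.** The strongest reply is that superiority names a hypothesis framework, as against equivalence or non-inferiority, and that Study design glosses it simply as a randomised two-arm comparison. A small early-phase trial can have a superiority hypothesis, so the two words are not contradictory in themselves. This stands. The mismatch comes from the combination of efficacy-only objectives, significance thresholds and proof language with a feasibility-based phase-I size. The word superiority alone does not create it.

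The feasibility basis is also openly disclosed, and the Conclusion is hedged with a conditional verb. Both are true. Disclosure does not make the basis fit the claim, however, and the hedge concerns whether benefit will be proven, not whether a trial of this size is meant to prove it.

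Some stronger readings are tempting but not supported:

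- **That the trial is declared confirmatory.** The article never uses the word.
- **That it is shown to be underpowered.** With no alpha, SD or target difference this cannot be established; 20 per arm suffices if the added effect is about 0.9 SD or more. The SD unit is also open. If change scores are tested and the baseline–outcome correlation is assumed to be 0.7, the SD of change is √(2 × 0.3) = 0.775 of the raw SD, so 0.91 SD of change is about 0.70 raw SD.
- **That a moderate effect could not be seen.** Power of 34% at 0.5 SD is low but not zero.
- **That seven primary scales are settled.** Variables to be measured lists seven, but the end of the Introduction makes the Barthel index, Ashworth scale and NIH stroke scale secondary, leaving Fugl-Meyer, single-limb stance and functional reach in the main goal. Splitting alpha would raise the 80%-power difference to 1.17 SD with seven scales or 1.06 SD with three. No split is planned, so both figures are hypothetical.

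**Conclusion.** The concern holds as a mismatch between the stated basis for the sample size and the stated purpose of the trial. Its size can be given only under assumptions: with a two-sided 5% unpaired t-test and 20 per arm, 80% power requires about 0.91 SD, power at 0.5 SD is about 34%, and the 95% confidence interval is about ±0.64 SD, slightly wider if the arms are unequal. The article offers no ground for expecting an added effect near 0.9 SD over a control arm that itself receives drug treatment and physiotherapy five days a week. That is a reason for caution, not proof that the trial is too small. Forty patients is not wrong in itself; it is a reasonable number for an exploratory estimate. It does not support the verdict on efficacy for which the text prepares the reader.

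**What to change.** Keep 40 patients and make the text consistent:

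- **Study design and Sample size:** remove the phase-I label. Describe the study in both places as an exploratory (pilot) randomised comparison with a superiority-type hypothesis.
- **Sample size:** add that, assuming a two-sided 5% unpaired t-test and 20 per arm, the design has 80% power for a difference of about 0.91 SD and gives a 95% confidence interval of about ±0.64 SD. Mark these as approximate and dependent on those assumptions.
- **Data section:** make between-group differences with 95% confidence intervals the main result. Stop using the 20% to 35% improvements as the rule for calling a result significant.
- **Variables to be measured and Introduction:** reconcile the seven-scale primary list with the secondary goal. The Introduction's goals also leave quality of life unplaced.
- **Introduction and Conclusion:** replace the aim of showing excellent recovery and the language of proof with a statement that the trial will estimate the added effect to inform a later confirmatory trial.

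This is wording in several sections and needs no extra patients. The price is a less favourable stated claim. If the sponsor prefers to keep a superiority conclusion, the alternative is to name one primary outcome and time point and size the trial from a justified between-group difference, SD, alpha and power. Under the assumptions above, a 0.5 SD target would need 64 per arm for 80% power.
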